### Data collection and measures

Data collection will include three-time points: at the beginning of the sessions funded by the Psychological Bonus (T0), at the end of the sessions funded by the Psychological Bonus (T1), and at six months follow-up (T2).

Figure 1 illustrates the data collection process and measured variables.

**Fig. 1 Fig1:**
[figure not shown]
PsyCARE study flowchart. Note: **DSM**: Diagnostic and Statistical Manual of Mental Disorders Text Revision (APA, 2022); **GAF**: Global Assessment Functioning (GAF; Moos et al., 2002; Pedersen & Karterud, 2012); **CORE-10**: Clinical Outcomes in Routine Evaluation 10 (Barkham et al., 2013; La Tona et al., 2023); **YP-CORE**: Young Persons’ Clinical Outcomes in Routine Evaluation 10 (Twigg et al., 2016; Di Biase et al., 2021); **ERQ**: Emotion Regulation Questionnaire (Gross and John, 2003; Balzarotti et al., 2010); **ETMCQ**: Epistemic Trust, Mistrust and Credulity Questionnaire (Campbell et al., 2021; Liotti et al., 2023); **GAD-7**: Generalized Anxiety Disorder Scale (Spitzer et al., 2006); **PHQ-9**: Patient Health Questionnaire-9 (Kroenke et al., 2001); **EQ-5D**: Euro Quality Of Life 5D (Stolk et al., 2010; Balestroni & Bertolotti, 2012); **EQ-5D-Y**: Euro Quality Of Life Youth 5D (Wille et al., 2010; Scalone et al., 2011); **YSR**: Youth Self-Report (Achenbach, 1991); **CPPS**: Comparative Psychotherapy Process Scale (Hilsenroth, et al., 2005; Gentile et al., 2020)

Variables explored will vary according to the data collection phase.

### Therapists’ recruitment

After providing informed consent, therapists will provide demographic data such as gender, age, and information on years of professional experience, primary theoretical orientation, and primary activity settings (i.e., in person, online, or both).

### Patients’ recruitment and baseline assessment (T0)

#### Therapists assessment at T0

After an initial consultation with new patients or when starting the sessions funded by the PB for patients already in treatment, therapists will provide a baseline assessment of their patients providing demographic data, number of sessions already conducted, reason for contact, clinical history (i.e., previous psychological support), and diagnostic information [32].

The *Global Assessment of Functioning Scale* (GAF) [33–35] will also assess the patient’s overall mental well-being, from severe mental health disorders to optimal mental health. The GAF score falls between 1, indicating the most extreme illness, and 100, indicating optimal mental health. The scale is split into ten segments, starting from 1 to 10 and ending at 91 to 100. A score of 70 or above identifies minimal impairment, while scores below 60 indicate severe impairment.

#### Adult patients assessment at T0

After providing informed consent, patients aged > 18 will provide demographics, information on productivity (i.e., how many days of work/university/school did you lose because of your psychological problems?), and self-report on psychological distress, emotion regulation, anxiety and depression symptoms, epistemic trust, and quality of life.

The *Clinical Outcomes in Routine Evaluation-10* (CORE-10) [36] is a brief 10-item measure to explore psychological distress developed for routine use in practice settings. The CORE-10 is a shortened version of the 34-item CORE-OM [37]. It taps into three domains: i) problems: depression (2 items), anxiety (2 items), physical (1 item), and trauma (1 item); ii) functioning: general functioning (1 item), social functioning (1 item), and close relationships (1 item); and iii) risk: to self (1 item). In addition, two items (i.e., item 2, ‘I have felt I have someone to turn to for support when needed’ and item 3, ‘I have felt able to cope when things go wrong’) are worded positively and thus are reverse scored. Items are rated on a 5-point Likert-type scale (0 = not at all to 4 = most or all of the time), and higher total scores (i.e., the sum of all items, ranging from 0 to 40) indicate greater distress. The CORE-10 has been validated on the Italian population [38].

The *Emotion Regulation Questionnaire* (ERQ) [39] is a ten-item questionnaire measuring two emotion regulation strategies. Cognitive Reappraisal (six items) is a cognitive strategy consisting of the attempt to change the emotional impact of a situation by reinterpreting its meaning (e.g., “When I want to feel less negative emotion, I change the way I am thinking about the situation”). By contrast, Emotional Suppression (four items) directly targets expressive behavior as it consists of the attempt to inhibit the overt expression of emotions (e.g., “I control my emotions by not expressing them”). Instructions ask the respondent “some questions about your emotional life, in particular, how you control (that is, regulate and manage) your emotions.“ The ten items are rated on a Likert scale ranging from one (strongly disagree) to seven (strongly agree). For our study we will use the Italian adaptation of the ERQ as a reference [40].

The *Generalized Anxiety Disorder Scale-7* (GAD-7) [41, 42] is a 7-item, 4-point rating scale developed to assess how frequently the patient has experienced seven anxiety symptoms during the last two weeks: [1] feeling nervous or anxious; [2] being able to stop or control worrying; [3] worrying too much about different things; [4] difficulty relaxing; [5] being restless; [6] feeling easily annoyed or irritable; and [7] feeling frightened as if something terrible might happen. The response options are not at all (score = 0), several days (score = 1), more than half of the days (score = 2), and nearly every day (score = 3). In addition, an item is included to assess the duration of anxiety symptoms. The total GAD-7 score ranges from 0 to 21, with higher values indicating more anxiety symptoms. For this study, we used the Italian version of the GAD-7, which was recently tested during the COVID-19 pandemic [43].

The *Patient Health Questionnaire-9* (PHQ-9) [44] is a 9-item, 4-point rating scale developed to assess depressive symptoms the patient has experienced in the last two weeks. The response options are not at all (score = 0), several days (score = 1), more than half of the days (score = 2), and nearly every day (score = 3). The total PHQ-9 score ranges from 0 to 27, with higher scores indicating more severe symptoms. The PHQ-9 validity has been confirmed on the Italian population [43, 45].

The *Epistemic Trust, mistrust, and Credulity Questionnaire* (ETMCQ) [28] is a 15-item self-report questionnaire assessing Epistemic Trust, Mistrust, and Credulity toward communication or communicated knowledge. Epistemic trust refers to an adaptive attitude in relatively benign social circumstances in which the individual is selectively and appropriately open to social learning opportunities in relationships. Epistemic Mistrust reflects the tendency to treat any source of information as unreliable or ill-intentioned, trying to avoid being influenced by the communication of others. Epistemic credulity refers to a marked lack of vigilance and discrimination, signaling a general lack of clarity about one’s position and resulting in vulnerability to misinformation and the potential risk of exploitation. Higher scores indicate a higher presence of the relative trait for each factor. For our study we will use the Italian adaptation of the ETMCQ as a reference [46].

*The Euro Quality Of Life-5D* (EQ-5D) [47] is an instrument that evaluates the quality of life. The EQ-5D descriptive system is a preference-based health-related quality-of-life measure with one question for each of the five dimensions: mobility, self-care, usual activities, pain/discomfort, and anxiety/depression. The answers given to EQ-5D yield 243 unique health states or can be converted into an EQ-5D index, a utility score anchored at zero for death and one for perfect health. The questionnaire includes a Visual Analog Scale (VAS) by which respondents can report their perceived health status with a grade ranging from 0 (the worst possible health status) to 100 (the best possible health status). The EQ-5D has been validated on the Italian population [48].

#### Adolescent patients assessment at T0

After collecting informed consent from both adolescents and their parents, patients aged between 14 and 18 will provide demographics, information on productivity (i.e., how many days at school did you lose because of your psychological problems?), and self-report on psychological distress behavioral problems, emotion regulation (ERQ), epistemic trust (ETMCQ), and quality of life.

The *Young Persons’ Clinical Outcomes in Routine Evaluation* (YP-CORE) [49] is a brief 10-item measure to explore psychological distress in adolescents. Items are inspired by the CORE-OM and explore general well-being, symptoms/problems, functioning, and risk for the self. The questions all focus on how the person has felt in the past week. Each question has five possible answers, ranging from 0 = “Not at all” to 4 = “Most or all of the time”. The total clinical score is the sum of all scores (range 0–4) ranging from zero to 40. For our study, we wil reference the Italian validation of the YP-CORE [50].

The *Youth Self Report* (YSR) [51] is a 112-item self-report measure that assesses general psychological and behavioral difficulties. The YSR is the most widely used scale for assessing behavioral problems in adolescence, supported by excellent psychometric properties [52] Each item is scored on a 3-point scale (0= “not true” to 2= “very or often true”). The measure yields a Total Problems score of general pathological functioning and two comprehensive subscales of Externalizing behavior problems and Internalizing problems. The Externalizing scale encompasses the subscales of Aggressive behaviors and Rule-breaking behaviors. The Internalizing scale includes the Anxious/Depressed, Withdrawn/Depressed, and Somatic Complaints subscales. For this study, we will utilize the Externalizing and Internalizing problems scales and the Thoughts problems scale (e.g., strange behaviors, hallucinatory experiences, sleeping less). Higher scores indicate higher problems in the specific dimension.

*The Euro Quality Of Life-5D-Youth* (EQ-5D-Y) [47] encompasses five items exploring adolescents’ quality of life exploring their perceived level of problems (no difficulty, some difficulty, a lot of difficulty) in mobility, self-care, usual activities, pain or discomfort and anxiety or depression. The questionnaire includes a Visual Analog Scale (VAS) by which respondents can report their perceived health status with a grade ranging from 0 (the worst possible health status) to 100 (the best possible health status). The EQ-5D-Y has been validated on the Italian population [53].

### Post-intervention assessment (T1)

#### Therapists assessment at T1

At the end of the sessions funded by the PB, therapists will provide a post-intervention assessment of their patients providing diagnostic information [54], an evaluation of the patient’s overall mental well-being (GAF), information on their satisfaction level regarding the Bonus measure and on more technical aspects of their intervention.

The *Comparative Psychotherapy Process Scale* (CPPS) [55] is a 20-item self-report measure that can be used by clinicians, patients, or external observers, to assess the therapist’s techniques during a session highlighting psychodynamic-interpersonal techniques (PI; include psychodynamic, psychodynamic-interpersonal, and interpersonal therapy) and cognitive-behavioral techniques (CB; include cognitive, cognitive-behavioral, and behavioral treatment) on a 7-points Likert scale (0 = “Not characteristic” to 6 = “Extremely characteristic”). For our study, we will reference the Italian validation of the CPPS [56].

#### Adult patients assessment at T1

At the end of the sessions funded by the PB, patients aged > 18 will provide information on productivity (i.e., how many days of work did you lose because of your psychological problems?) and self-report on psychological distress (CORE-10), emotion regulation (ERQ), anxiety (GAD-7) and depression symptoms (PHQ-9), epistemic trust (ETMCQ), quality of life (EQ-5D), and level of satisfaction regarding the Bonus measure.

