### Follow-up assessment after six months (T2)

Six months after the end of the sessions funded by the PB, therapists will provide information on the continuation vs. interruption of their psychological interventions and eventually report on their patients’ diagnosis (APA, 2022) and overall mental well-being (GAF).

Adult patients will report on productivity, psychological distress (CORE-10), emotion regulation (ERQ), anxiety (GAD-7) and depression symptoms (PHQ-9), epistemic trust (ETMCQ), and quality of life (EQ-5D). Adolescent patients will report on productivity, psychological distress (YP-CORE), behavioral problems (YSR), emotion regulation (ERQ), epistemic trust (ETMCQ), and quality of life (EQ-5D-Y).

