To assess the economic impact of the PB (Objective 3), we will conduct a cost-effectiveness analysis (CEA) [64]. The calculation will include both direct and indirect costs between the baseline (T0) and post-intervention (T1) assessments. Direct healthcare costs will encompass the costs of the psychological intervention and any related healthcare costs. These costs will be compared to data on standard care from the Italian Ministry of Health to calculate the incremental costs of the intervention. Indirect costs, or productivity losses, will be estimated by multiplying the number of days of work/university/school lost due to psychological problems (as reported by participants) by an average daily wage (for work) or an estimated cost of a lost day of education (for university/school). The effectiveness of the intervention will be measured using the EQ-5D, which will be used to estimate Quality Adjusted Life Years (QALYs). The incremental cost-effectiveness ratio (ICER) will be calculated as the cost difference between the PB intervention and standard care from T0 to T1, divided by the difference in QALYs over the same period. The resulting ICER will represent the additional cost per QALY gained by the PB intervention compared to standard care. A sensitivity analysis will be conducted to test the robustness of our findings to changes in key assumptions or parameters, including the unit costs used to calculate direct costs and the valuation of lost productivity. This analysis will be conducted in accordance with standard guidelines for conducting and reporting CEAs, such as the Consolidated Health Economic Evaluation Reporting Standards (CHEERS) statement [65]. The power analysis from the *pwr* package in R [66] indicated that for a paired t-test with a small effect size (Cohen’s d = 0.20), a power of 0.80, and a significance level α = 0.05, you would need a sample size of approximately n = 199 pairs of observations.

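### For adults, the T1 productivity item covers work days only, while the T0 item and the costing rule also cover university and school days

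*Protocol article*

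**What the plan says.** Three places in the protocol article bear on this point.

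- **Adult patients assessment at T0.** Adults report productivity as "how many days of work/university/school did you lose because of your psychological problems".
- **Adult patients assessment at T1.** The same patients are asked "how many days of work did you lose because of your psychological problems". University and school are no longer named.
- **Data analyses, Objective 3.** "The calculation will include both direct and indirect costs between the baseline (T0) and post-intervention (T1) assessments". Indirect costs come from "multiplying the number of days of work/university/school lost due to psychological problems (as reported by participants) by an average daily wage (for work"), with a separate estimated cost for a lost day of education.

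For adolescents the item is "how many days at school did you lose because of your psychological problems" at T0, and the T1 section repeats it unchanged. At T2 adults again report productivity, with no item wording printed, along with "epistemic trust (ETMCQ), and quality of life (EQ-5D").

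**The concern.** The costing rule needs a count of study days lost by adults between T0 and T1, and the T1 item as printed does not ask for it. Adults in the study include anyone over 18, and the T0 wording itself expects some of them to be at university or school.

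The cost-effectiveness analysis is one of the primary aims, and Hypothesis 3 expects productivity to improve. A question that is broader before the sessions than after them tends to produce that improvement by itself. The Discussion says the results may help justify future funding, so an artefact that favours the policy should be removed. The sensitivity analyses named for Objective 3 vary unit costs and the value placed on lost productivity. Neither can restore days that were never asked about.

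**Working it through.** **1. The plan's own figure.** The only number given for Objective 3 is about 199 pairs for a paired t-test with d = 0.20, power 0.80 and α = 0.05. Using the noncentral t distribution and a two-sided test, n = 198.15, which rounds up to 199. The figure reproduces, and this point does not affect it. The article gives no lost-day counts, wages, utilities or ICER, so the effect on cost can only be illustrated.

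**2. The items side by side.**

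| Group | T0 item | T1 item | Costed over T0-T1 |
|---|---|---|---|
| Adults | work, university, school | work | work, university, school |
| Adolescents | school | school | school |

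Only the adult T1 cell fails to match its row.

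**3. Two readings of the costing rule.** Write W for an adult's lost work days and E for lost study days, with subscripts 0 and 1 for the T0 and T1 reports. Let s = E/(W + E) be the study share, w the daily wage and e the cost of a lost education day.

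- *Before-after reading*, implied by the productivity expectation in Hypothesis 3 and by the paired t-test. The T0 count is W₀ + E₀ and the T1 count is W₁. With no true change (W₁ = W₀, E₁ = E₀), the apparent change is W₁ − (W₀ + E₀) = −E₀. As a fraction of the T0 count this is −s.
- *Within-window reading*, the literal sense of costs between T0 and T1. The T0 item is answered at the start of the window, so only the T1 item can describe it. True indirect cost is W₁w + E₁e, counted cost is W₁w, and the shortfall is E₁e. As a fraction this is s·e / [(1 − s)·w + s·e], which equals s when e = w.

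Under both readings the adult count at T1 is too low, which lowers the Bonus side's indirect cost.

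**4. Size.** The article does not give s. For assumed values:

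| s (assumed) | Apparent fall in counted days, no true change |
|---|---|
| 0.10 | 10% |
| 0.20 | 20% |
| 0.30 | 30% |
| 0.50 | 50% |

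In cost terms the fraction also depends on e relative to w, which the article leaves open.

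**5. Horizon, checked separately.** Assume a utility gain g that builds linearly over a T0-T1 window of L years, with a fraction k kept at T2 half a year later. QALYs to T1 are 0.5·g·L. QALYs to T2 add 0.5·(g + kg)·0.5. The ratio is 1 + 0.5·(1 + k)/L, whatever g is.

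- L = 28/365.25: 14.0 for k = 1 and 7.5 for k = 0.
- L = 180/365.25: 3.0 for k = 1 and 2.0 for k = 0.

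These ratios show how much a T1 horizon leaves out under the assumptions. They are not factors by which the ICER would shrink, because costs from T1 to T2 would also have to be added.

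**The case against.** The strongest defence is that both items stand in parentheses in a condensed article and the questionnaire is not shown. The Objective 3 text speaks of work, university and school days as reported by participants, so the T1 wording may be shorthand for the full item. That is possible. It is weakened because the parentheses give the question itself and the adolescent item is repeated without change. The passages disagree as printed and need reconciling either way.

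It is also fair that the ICER rule does not state that T0 days are subtracted from T1 days. Step 3 of the working covers this: the within-window reading fails too, because the T1 item is then the only source.

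Three stronger inferences are tempting and are not supported.

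- *That the counts are not comparable because no recall period is printed.* A recall period is detail that an article may leave to the questionnaire, so its absence here shows nothing. The 180-day limit runs from approval of the bonus, not from T0, so it does not fix the window either.
- *That ending at T1 distorts the ICER or throws away the T2 data.* The T0-T1 horizon is stated consistently in the aims, in Hypothesis 3 and in the analysis section. Costs are set against QALYs on a matched basis, "divided by the difference in QALYs over the same period". A short horizon limits what the ratio covers but does not make it wrong. The abstract's description of the analysis as longitudinal sits loosely with it, but the text nowhere says the T2 utilities go unused in the study.
- *That a euro figure can be attached.* Any such figure would need an invented utility gain and incremental cost.

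**Conclusion.** The point holds for adults only. The T0 item, the T1 item and the costing rule do not agree, and as printed the T1 item cannot supply the study-day input that the analysis costs. The Bonus side's indirect cost can be understated, and a productivity gain can appear without true change. Both errors favour the policy.

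The size equals the study share of adult lost days: 10% to 50% of counted days over an assumed range of 10% to 50%, with study days lost at an unchanged rate and not reported at T1. The documents fix neither that share nor the cost of an education day relative to a wage. It follows that indirect costs *can* be distorted, not that they *are*. The effect on the ICER depends further on whether the standard-care data include education losses, which the article does not say. If the questionnaire actually used at T1 names all three settings, the remedy is a correction of the text.

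**What to change.** 1. Check the T1 questionnaire in use. If it already covers university and school, correct the T1 section and stop there.
2. Otherwise use the same work, university and school item for adults at T0, T1 and T2. Record work days and study days in separate fields, and have the T1 item refer to the T0-T1 interval that the analysis costs.
3. For adult records already collected with the work-only T1 item, restrict the productivity comparison to work days at both times where the T0 answer allows the split. If T0 days were pooled, restrict it to adults who are not students, provided the T0 demographics identify them. State in the report that education losses are not covered for these records. Converting existing counts to a rate is not proposed, since the article prints no reference period to serve as a denominator.
4. Optionally, add a T0-T2 ICER as a sensitivity analysis, using the EQ-5D and productivity data collected at T2 and including T1-T2 costs. Therapists' T2 reports are described only as continuation or interruption, so session numbers and prices after T1 would also be needed. This extends the pre-specified T0-T1 analysis; it does not correct an error.

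The cost is an edit to one online item and a note in the analysis. Because data collection is already under way, the data will contain two versions of the item, and early adult records lose the study-day component. The optional analysis would rest on fewer patients if some are lost before T2.

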#### Adolescent patients assessment at T1

At the end of the sessions funded by the PB, patients aged between 14 and 18 will provide information on productivity (i.e., how many days at school did you lose because of your psychological problems?) and self-report on psychological distress (YP-CORE), behavioral problems (YSR), emotion regulation (ERQ), epistemic trust (ETMCQ), quality of life (EQ-5D-Y), and level of satisfaction regarding the Bonus measure.

